### Power and sample

The study power calculation is based on opportunities to detect an impending increase in adherence to national bladder monitoring guidelines: assuming an absolute increased adherence to the guidelines of 15% (50% in the control group and 65% in the intervention), the required sample size is 227 patients in each arm, with 90% power and two-sided significance level of 0.05 (based on an intracluster correlation coefficient of 0.03). With 10 clusters in each arm and an average cluster size of 70 patients, a total of 1380 patients are needed. Considering a dropout rate of 10%, a total sample size of 1500 is required, providing an average cluster size of 75 patients. With a variance between around 5% and 80% incidence of urinary retention among hip surgery patients, it is difficult to calculate power based on this factor. Yet, considering that it may be 35–40%, the cluster size suggested above will also allow detecting a 15% absolute difference in incidence of urinary retention between the intervention group and the control group post intervention.

Once the units had agreed and the ethics board had approved the trial, the randomisation was performed. To prevent bias in terms of complexity of the patients’ medical status, and influence of clinical training programmes for students in nursing science and physio- and occupational therapy, university hospitals were equally distributed as intervention and control units. Further, two units located in Stockholm, the capital of Sweden, were randomised to either intervention or control. Thus, the randomisation was completed in four steps: university units, units in the Stockholm catchment area, and regional orthopaedic and local orthopaedic units, respectively, drawn from sealed envelopes by an impartial researcher engaged for this procedure whilst monitored over video link by the research team.

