### Participants

#### Patients

Patients undergoing hip surgery in any of the orthopaedic units (whether control or intervention groups) during the project’s three data collection points will be informed about and asked to participate in the study at baseline and follow-ups I and II. Although the risk for urinary retention increases with age, and most hip surgery patients are becoming of advanced age, we will not exclude younger patients and thus discriminate due to age. Rather, inclusion criteria besides being admitted for hip surgery encompass the ability to communicate in Swedish without an interpreter, whilst a diagnosed cognitive impairment is an exclusion criterion.

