### Data collection

The primary outcome measure for OPTION is:
Adherence to urinary retention guidelines in the care of patients undergoing hip surgery.

Additional outcomes are:
A.Incidence of and severity of urinary retention, bladder distension, and voiding complications among hip surgery patients (WP1, WP4 and WP5).B.Activities and experiences of urinary retention, bladder distension, and voiding complications care among nursing and rehabilitation staff in orthopaedic care (WP1, WP3, and WP5).C.The IFs’ and managers’ experiences of the facilitation programme (WP2 and WP5).D.The patients’ experience of bladder care and voiding self-care management during the hospital stay and post discharge, including conditions for participating in these health-related issues (WP1, WP4, and WP5).E.Use and costs of urinary retention devices and labour related to bladder monitoring (WP5).

Hence, data will be collected as follows:

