### Data analysis

Data from patients’ records, the Alberta Context Tool questionnaire, the patient survey on voiding difficulties, and patient participation will be analysed with statistical analyses [46]. Between-group differences will be analysed using Student’s independent-sample t test for continuous variables, the Mann–Whitney U test for non-normally distributed continuous variables, and a χ2 test for nominal variables.

Qualitative content analysis will be applied for all interviews [47, 48], subsequently transcribed verbatim to text files by a professional service.

All data will be considered in the final mixed methods [49], embedding the process evaluation [50].

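### The χ2 test named for nominal outcomes cannot use age, which the article itself calls a risk factor for retention; the cost is some precision on an additional outcome, not bias

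*Protocol article*

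**What the plan says.** Under Participants, Patients, the article sets no age limit and says that although "the risk for urinary retention increases with age, and most hip surgery patients are becoming of advanced age, we will not exclude younger patients".

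Under Data collection, the primary outcome is "Adherence to urinary retention guidelines in the care of patients undergoing hip surgery". Retention belongs to additional outcome A: "Incidence of and severity of urinary retention, bladder distension, and voiding complications among hip surgery patients". Its data come from patient records.

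Under Data analysis, which covers patient-record data, the text reads "Between-group differences will be analysed using Student’s independent-sample t test for continuous variables", then gives the Mann–Whitney U test for non-normal continuous variables and a "χ2 test for nominal variables". It names no regression model, covariate or adjusted comparison.

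Under Power and sample, the article states that the chosen cluster size will "allow detecting a 15% absolute difference in incidence of urinary retention between the intervention group and the control group post intervention", taking incidence as 35–40%. The same section describes randomisation in four steps by type or location of unit (university, Stockholm, regional, local). Age is not one of them. Under Setting and inclusion criteria, sites doing fracture and elective surgery and sites doing elective surgery only are treated as equal.

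**The concern.** The article identifies one patient-level prognostic factor for retention, lets it vary without limit, and then names a test that cannot use it. That goes a step beyond leaving a covariate list open.

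Only 20 units are randomised, and their surgical mix may differ, so the mean age of patients can differ between arms by chance. If age predicts retention, part of the between-site variance is age-driven. An analysis without age leaves that part in the error term. An analysis with age removes it and corrects the estimate for whatever age difference the actual allocation produced. At stake is precision on outcome A. The article claims no age effect for the primary outcome.

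**Working it through.** **Inputs from the article (Power and sample).** Adherence 50% v 65%; 227 per arm before clustering; 90% power; two-sided 0.05; ICC 0.03; 10 sites per arm; 70 patients per site; 1380 in total, 1500 with dropout (75 per site); retention 35–40% with a 15-point difference.

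**Assumed inputs (not in the article).** Odds ratio for retention of 1.3 or 1.5 per 10 years of age; between-site SD of mean age of 2, 4 or 6 years; within-site SD of age of 12 years.

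**1. The article's own figures.** The two-proportion formula for 50% v 65% (pooled, no continuity correction) gives 227 per arm. With a design effect of 1 + (m − 1) × 0.03, m = 69 gives 2 × 227 × 3.04 = 1380. The sample size reproduces.

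**2. Power for retention without age, by formula.** With m = 70 the design effect is 1 + 69 × 0.03 = 3.07, so the effective size per arm is 700/3.07 = 228. Power is 95% for 35% v 20% and 93% for 40% v 25%. The claim of adequate power for a 15-point difference holds without any age term.

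**3. Chance age imbalance.** The difference between arms in mean age has SD = (between-site SD) × √(2/10), ignoring sampling of patients within sites. A one-SD imbalance shifts the unadjusted retention difference by about ln(OR)/10 × imbalance × 0.375 × 0.625.

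| Between-site SD (years) | SD of arm difference (years) | Shift, OR 1.3 (points) | Shift, OR 1.5 (points) |
|---|---|---|---|
| 2 | 0.89 | 0.55 | 0.85 |
| 4 | 1.79 | 1.10 | 1.70 |
| 6 | 2.68 | 1.65 | 2.55 |

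In the middle case (SD 4, OR 1.5) the 95% range is 1.96 × 1.70 = ±3.3 points, against a 15-point target.

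**4. Precision.** The simulation used 20 sites of 75. Total site variance on the logit scale was 0.03/0.97 × π²/3 = 0.102, split into an age-driven part, (log OR per year × between-site SD)², and a residual. It compared a t test on site proportions with a t test on site means of residuals from a logistic model on age fitted without arm. With OR 1.5 and retention of 37.5% v 25.5%, the standard errors were:

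| Between-site SD (years) | SE without age | SE with age | Reduction |
|---|---|---|---|
| 2 | 0.0379 | 0.0366 | 3% |
| 4 | 0.0375 | 0.0342 | 9% |
| 6 | 0.0371 | 0.0298 | 20% |

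Those rates differ by 12 points. At the article's 15 points, power without age is 97–98% in all six settings (two odds ratios, three SDs). Adding age gains from under 1 to about 3 points. Over the six settings the SE reduction runs from about 2% to 21%.

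This power is above the 93–95% of step 2 chiefly because an ICC of 0.03 on the logit scale is smaller on the proportion scale: about 0.102 × 0.375 × 0.625 = 0.024 in the control arm and 0.102 × 0.225 × 0.775 = 0.018 in the intervention arm. Both figures show ample power.

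**5. Type I error.** With no effect, the site-level test without age rejects in about 4–6% of runs, so it is valid. The plain χ2 test rejects in about 21–24%. The design-effect calculation, 2 × (1 − Φ(1.96/√3.07)), gives 26%. That excess comes from ignoring clustering, and an age term would not cure it.

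**The case against.** The strongest objection is that covariates for an additional outcome are normally left to the analysis plan, that the Data analysis section is a short generic list which never mentions retention by name, and that age appears only to justify broad eligibility. This stands in part: an unnamed covariate list would be no finding. But retention incidence is a nominal outcome from patient records, so the listed rule applies to it, and the named test cannot take a covariate. Improving a stated method is a fair suggestion.

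A reader might infer that the unadjusted comparison is biased, because a chance age difference would be taken for an effect of the programme. The documents do not support that. Units were randomised, so chance age differences average out over allocations. They are part of the between-site variance that a site-level analysis already counts, as its 4–6% rejection rate shows.

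A reader might also infer that retention is underpowered without age. At the article's own target it is not. Larger gains appear if the age-driven variance is added on top of an ICC of 0.03: with OR 2.0 and a between-site SD of 6 years, power goes from 71% to 95%. But the total ICC is then about 0.08, which is not the article's figure.

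Two further cautions stand. At OR 1.5 and SD 6, age is assumed to explain (0.0405 × 6)²/0.102 = 58% of all between-site variance, which no figure in the article supports. And the simulation contains no surgery type, randomisation strata or baseline site rates. Any of these could absorb part of what age explains, so the added value of age beyond them is untested.

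**Conclusion.** The point holds as a modest matter of efficiency. The article names age as a risk factor for retention, admits all ages, and states a test that cannot use age. The comparison of outcome A therefore loses some precision and is not corrected for the age difference that the actual allocation of 20 sites happens to give.

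On the assumed inputs, the SE reduction is about 2% to 21%, and the power gain at a 15-point difference is at most about 3 points from a base of about 97–98%. The between-site spread of mean age matters most, and the documents do not give it. The weakest setting is close to negligible.

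The point concerns an additional outcome and leaves the primary comparison of adherence untouched. It is also secondary to the larger weakness of the same χ2 test, which ignores clustering although the sample size assumes an ICC. The age term is worth having only once that is repaired. Priority: an optional improvement at almost no cost.

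**What to change.** In the Data analysis section, or in the analysis plan with a reference from it, state that retention, bladder distension and voiding complications will be compared between arms in an analysis that respects sites. Examples are a mixed logistic model, GEE with a small-sample correction, or a two-stage site-level analysis. Prespecify patient age in it as a continuous covariate.

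Report the result as an age-standardised risk difference, so that the quantity estimated stays the absolute difference used under Power and sample. Keep the unadjusted site-level comparison as a sensitivity analysis. Fix this wording before outcomes are compared between arms, so that the adjustment cannot appear to have been chosen after seeing results.

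The cost is a sentence or two. Age should be available from the patient record, though the record template is not shown and this should be confirmed. One patient-level covariate uses almost none of the site-level degrees of freedom.

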#### Staff

All nursing and rehabilitation staff employed in the intervention and control units, respectively, are informed about the study; thus, registered nurses, licensed practical nurses, physiotherapists, and occupational therapists are invited to take part in the three data collection points, with the exclusion of those on long-term absence (e.g. parental or sick leave).

#### Managers

All managers of nursing and rehabilitation staff are likewise informed about the study and invited to take part in the data collection.

#### Internal facilitators

The staff assigned as internal facilitators (IFs) are recruited by the intervention units themselves, according to a document providing a background regarding facilitation, the IF’s qualifications in general and in OPTION, and suggesting selecting IFs based on:
An interest in urinary retention and/or an interest in and ability to support others in evidence-based practice,A formal or informal leader recognised to enable improvement efforts,Being inclined to problem-solving and reflection, and,Being willing and capable of collaborating and learning.

The IFs are expected to take on their role for the 12-month intervention period and thus to hold a permanent employment position.

#### First-line managers

The first-line managers of the nursing and rehabilitation staff, respectively, will be expected to join the IF teams for the 12-month intervention period in the intervention units.

### The implementation object

The Handbook for Healthcare is a quality-assured resource for all healthcare workers and organisations across Sweden. It is provided by the Swedish Association of Local Authorities and Regions, that is, the public sector body for all health and medical services and social services. It comprises 122 chapters on fundamentals of care, including basic and advanced procedures. Whilst formerly a printed book, it has been online since 2002: vardhandboken.se. One of the chapters is ‘Bladder monitoring in hospital care’, including eight sections: an overview, symptoms and diagnosis of bladder extension, ultrasound with a portable bladder scan, assessment and interventions when a risk of urinary retention, schedule for voiding monitoring, bladder monitoring during surgery procedures, references and regulations, and a knowledge self-test on the chapter and its sections. The current chapter was revised in 2019 by two experts, both senior researchers and clinical experts, and reviewed by two independent experts in the area, comprising nursing and medicine.

### The implementation strategy

The OPTION intervention builds on the renowned Integrated Promoting Action on Research Implementation in Health Services (i-PARiHS) framework [31, 32] and the Ottawa Model of Implementation Leadership, O-MILe [33–35]:

The OPTION study trials a multi-professional, multi-level strategy: the orthopaedic units in the intervention group select their teams as above and are expected to serve as facilitators as individuals and as a group, enabling others to adapt the guidelines and addressing attitudes and routines that can pose barriers to such adaptation, including de-implementation of outdated or redundant praxis [29]. The 10 intervention units will receive the support programme for teams, whilst the 10 control group units will receive no support. Nevertheless, both the intervention units and the control units have and have had unlimited access to guidelines as described above.

An overall plan for the events and timing is provided in Fig. 3.
E-meet and seminar. Half-day or full-day seminars for all IF teams (including first-line managers) via video link or face-to-face venues. Scaffolding the local team and overall team building, some sessions will be for both IFs and managers, and some separate, addressing more specifically the IFs in terms of the clinical issues re urinary retention and knowledge translation [36, 37] and the managers in implementation leadership [26–28]. The purpose is for the IFs and managers to learn and share, including progress and experiences.Web. Providing the teams with tools and sources via the unique web page which they can access 24/7, with opportunities to post queries, this will provide on-demand support during the intervention and also build a resource bank, including FAQs, on guideline implementation and de-implementation of low-value care related to urinary retention matters.Open space. Opportunities to meet with the researchers (i.e. external facilitators) to consider and settle local issues and processes for implementation of evidence-based urinary retention care.

**Fig. 3 Fig3:**

Overview of intervention timeline and activities

### Data collection

The primary outcome measure for OPTION is:
Adherence to urinary retention guidelines in the care of patients undergoing hip surgery.

Additional outcomes are:
A.Incidence of and severity of urinary retention, bladder distension, and voiding complications among hip surgery patients (WP1, WP4 and WP5).B.Activities and experiences of urinary retention, bladder distension, and voiding complications care among nursing and rehabilitation staff in orthopaedic care (WP1, WP3, and WP5).C.The IFs’ and managers’ experiences of the facilitation programme (WP2 and WP5).D.The patients’ experience of bladder care and voiding self-care management during the hospital stay and post discharge, including conditions for participating in these health-related issues (WP1, WP4, and WP5).E.Use and costs of urinary retention devices and labour related to bladder monitoring (WP5).

Hence, data will be collected as follows:
A.Quantitative data regarding urinary retention will be collected from patient records, including bladder monitoring, voiding and healthcare interventions, by means of a structured template [12, 22] at baseline, post completion of the study intervention, and an additional, 1-year follow-up.B.Structured patient record assessment in triangulation with qualitative interviews with a random sample of nursing and rehabilitation staff and managers across all sites [13, 23, 25, 38]. In addition, baseline data collection includes mapping the context, with the Alberta Context Tool (ACT) [39, 40] distributed among all nursing and rehabilitation staff.C.Qualitative interviews post intervention (follow-ups I and II), in addition to voice recordings of all events during the intervention (support programme) [13, 23, 41]. Further, IF teams and managers will be asked to keep notes, by means of an individual, semi-structured reflective diary [42].D.Structured patient record assessment in triangulation with a post-discharge structured survey to all hip surgery patients for voiding difficulties after the hospital episode, self-care management and conditions for participating in accordance with one’s preferences—the latter using the 4Ps tool (Patient Preferences for Patient Participation) [43–45]. Further, data will originate from qualitative interviews with a sample of two patients per data collection point and site, representing the age range and gender distribution among those having had hip surgery.E.The structured patient record assessments at baseline, follow-up I and follow-up II will inform the health economics evaluation.

### Data analysis

Data from patients’ records, the Alberta Context Tool questionnaire, the patient survey on voiding difficulties, and patient participation will be analysed with statistical analyses [46]. Between-group differences will be analysed using Student’s independent-sample t test for continuous variables, the Mann–Whitney U test for non-normally distributed continuous variables, and a χ2 test for nominal variables.

Qualitative content analysis will be applied for all interviews [47, 48], subsequently transcribed verbatim to text files by a professional service.

All data will be considered in the final mixed methods [49], embedding the process evaluation [50].

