**Methods:**

Twenty orthopaedic sites are cluster randomised into intervention and control sites, respectively. The intervention sites assemble local facilitator teams among nursing and rehabilitation staff, including first-line managers. The teams receive a 12-month support programme, including face-to-face events and on-demand components to map and bridge barriers to guideline implementation, addressing leadership behaviours and de-implementation of unproductive routines. All sites have access to the guidelines via a public healthcare resource, but the control sites have no implementation support.

Baseline data collection includes structured assessments of urinary retention procedures via patient records, comprising incidence and severity of voiding issues and complications, plus interviews with managers and staff, and surveys to all hip surgery patients with interviews across all sites. Further assessments of context include the Alberta Context Tool used with staff, the 4Ps tool for preference-based patient participation used with patients, and data on economic aspects of urinary bladder care.

During the implementation intervention, all events are recorded, and the facilitators keep diaries.

Post intervention, the equivalent data collections will be repeated twice, and further data will include experiences of the intervention and guideline implementation.

Data will be analysed with statistical analyses, including comparisons before and after, and between intervention and control sites. The qualitative data are subjected to content analysis, and mixed methods are applied to inform both clinical outcomes and the process evaluation, corresponding to a hybrid design addressing effectiveness, experiences, and outcomes.

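### The named between-group tests ignore site in a 20-cluster trial; at the planning ICC a nominal 5% test of adherence runs at about 26%

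*Protocol article*

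**What the plan says.** The Abstract (Methods) gives the design: "Twenty orthopaedic sites are cluster randomised into intervention and control sites, respectively". Power and sample sizes the trial on guideline adherence, at 50% in control sites and 65% in intervention sites. Before clustering, "the required sample size is 227 patients in each arm, with 90% power and two-sided significance level of 0.05". The calculation is "based on an intracluster correlation coefficient of 0.03", and the result is: "With 10 clusters in each arm and an average cluster size of 70 patients, a total of 1380 patients are needed". The allowance for loss follows: "Considering a dropout rate of 10%, a total sample size of 1500 is required, providing an average cluster size of 75 patients". The Data collection section makes adherence the primary outcome.

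The Data analysis section covers the patient records, the staff context questionnaire and the patient survey together. It chooses tests by type of variable: "Between-group differences will be analysed using Student’s independent-sample t test for continuous variables", then Mann–Whitney U where the data are not normal, "and a χ2 test for nominal variables". It mentions no random effect, GEE, robust variance, site-level summary or other allowance for site, and neither does the rest of the article.

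**The concern.** Patients at one site share staff, routines and managers, and the intervention acts on exactly those. Their outcomes are therefore correlated, and the plan accepts this by assuming a positive ICC. A chi-squared or t test on patients counts each patient as a separate piece of evidence about the intervention, although only 20 units were allocated.

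The plan thus enlarges the sample about threefold for clustering and then names tests that ignore it. Standard errors would be too small, p-values too small and any confidence interval built on them too narrow. The primary comparison is at stake, and so are the additional quantitative between-arm comparisons on patients or staff. The interview-based outcomes are not affected.

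**Working it through.** **Inputs (Power and sample):** proportions 50% and 65%; two-sided alpha 0.05; power 90%; ICC 0.03; 10 clusters per arm; about 70 patients per cluster; 1380 in total; 1500 after 10% dropout, or 75 per cluster.

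**Step 1: reproduce the plan's sample size.** The standard two-proportion formula (pooled variance under the null, no continuity correction) gives 227 per arm, as stated. The design effect is DE = 1 + (m − 1) × ICC. The total of 1380 over 20 sites is m = 69, so DE = 1 + 68 × 0.03 = 3.04 and 2 × 227 × 3.04 = 1380. The stated total is therefore the cluster-adjusted one. (1380/0.9 is 1534, close to the stated 1500.)

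**Step 2: error rate of a test that ignores site.** Such a test uses a variance too small by a factor DE, so its z statistic has standard deviation √DE under the null. The true two-sided level is

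α* = 2 × [1 − Φ(1.96/√DE)].

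| Patients per site | DE at ICC 0.03 | √DE | α* |
|---|---|---|---|
| 67.5 (1500 × 0.9 / 20) | 2.995 | 1.73 | 25.7% |
| 69 (1380 / 20) | 3.04 | 1.74 | 26.1% |
| 70 (as stated) | 3.07 | 1.75 | 26.3% |
| 75 (1500 / 20) | 3.22 | 1.79 | 27.5% |

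The √DE column is the factor by which the standard error is understated.

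**Step 3: simulation.** Null trials were simulated with 10 sites per arm, equal site sizes, beta-binomial site proportions with mean 0.5 and ICC 0.03, 200,000 trials per setting.

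| Patients per site | Chi-squared | Chi-squared, Yates | t test on 20 site proportions |
|---|---|---|---|
| 69 | 25.8% | 24.8% | 5.0% |
| 70 | 26.6% | 25.4% | 5.0% |
| 75 | 28.0% | 26.8% | 5.0% |

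**Step 4: sensitivity to the ICC** (formula, 70 patients per site): ICC 0.01 gives 13%, 0.02 gives 20%, 0.03 gives 26% and 0.05 gives 35%. Any positive ICC pushes the level above 5%.

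**Step 5: power of a valid test.** In simulation at 50% v 65% and ICC 0.03, the t test on site proportions has 86.6% power with 69 patients per site and 87.4% with 75.

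**The case against.** The article does not state the unit of analysis and ties no test to the primary outcome by name. A t test or Mann–Whitney test on 20 site summaries would be valid. That is fair as far as it goes: patient-level testing of adherence is an inference. It is a strong one. The section assigns tests by variable type to patient-record, questionnaire and survey data, a chi-squared test on a nominal variable is naturally read as a test on patients, and adherence is powered as a proportion of patients. Nothing says that site summaries are meant.

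A statistical analysis plan that is not shown might deal with clustering. Silence in an article could be excused on that ground. Here specific tests are named, and a valid analysis plan would have to depart from them.

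Three limits on the size do stand:

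- The 26% is two-sided. With no true effect, about half of the false rejections favour control, so a false claim of benefit would arise about 13% of the time, or one in eight.
- The figure assumes ICC 0.03, equal site sizes and unstratified allocation. Randomisation was done in four steps by type and location of unit, which may remove part of the between-site variance. If the strata took the effective ICC down to 0.02 (an assumption, not a figure in the article), the rate would be about 20%. Unequal site sizes would push it up.
- The 26% does not carry over to the staff questionnaire or the patient survey, for which no ICC is given. The direction of the error does.

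**Conclusion.** The point holds, and the wording must be corrected. The named tests, applied to patients or staff, contradict both the cluster randomisation and the cluster-adjusted sample size. At the planning ICC and 67.5 to 75 patients per site, standard errors are too small by a factor of about 1.7 to 1.8. A nominal 5% test of adherence then has a true two-sided error of about 26% to 28%. A programme with no effect would give a significant difference in one direction or the other about one time in four. This rests on the plan's own ICC and cluster sizes and on reading the chi-squared test as a patient-level test. The exact rate moves with the ICC, as shown above; the inflation does not go away for any positive ICC.

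**What to change.** Replace the three tests, for every between-arm comparison of patient- or staff-level data, with analyses that respect site. For adherence, prespecify one of the following as primary:

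- a t test on the 20 site proportions (20 − 2 = 18 degrees of freedom), or its regression form with the randomisation strata and baseline site adherence as covariates;
- a mixed model with a random site effect and small-sample degrees of freedom. Kenward–Roger and Satterthwaite belong to the linear mixed model; fitted to the 0/1 outcome, that model gives the risk difference directly. If a logistic model is preferred, say how the risk difference and its interval will be derived;
- GEE with a small-sample variance correction, since 20 clusters are too few for the uncorrected robust variance.

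Report the risk difference with a 95% confidence interval, and state how the four randomisation strata enter. Each covariate costs degrees of freedom: four strata take 3, leaving 15 for a site-level analysis, and baseline adherence takes one more, leaving 14. Fix the choice before any between-arm comparison is made.

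The change is to analysis wording only and needs no new data. Intervals become wider, by a factor of about 1.75 at the planning ICC, and valid. Power for the simple site-level t test is about 87% against the planned 90%; adjustment for baseline site adherence may recover some of this.
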